#### Analysis of primary outcomes

For the primary outcome of this trial, the clinical recovery time of no more than 28 days after the completion of therapy and follow-up will be estimated as the proportion with a 95% confidence interval (CI) for each treatment group. The difference between the control arm and the experimental arm will subsequently be determined using the log-rank test. In order to control the influence of possible confounding factors such as gender and age on the clinical recovery time, the Cox proportional hazard model will be used to compare whether the clinical recovery time of the two groups is different, provide HRs and 95% CIs.

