### Randomization

Grouping is carried out using a centrally stratified, randomized block method. Before the trial, a statistical expert will use SAS software to set the number of centers at four, the block size will be four, the number of blocks will be 28, using a 1: 1 ratio between the experimental group and the control group, will generate 112 random numbers and corresponding grouping information. According to the haphazard allocation table used in advance, the statistical expert gives random numbers (1–112) in ascending order. Each random number and grouping information correspond to an envelope. The envelope is sealed and given to the researchers responsible for screening. Qualified subjects are selected, and the envelopes are received in the order of enrollment. After the envelopes are opened, the random-number and grouping information is removed, so that the subjects will be randomly assigned to the experimental group or the control group, and the corresponding treatment and observations performed. Each subject’s random number is unique and remains the same throughout the trial.

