### Sample size

The hypothesis of this study is that the use of chloroquine phosphate instead of lopinavir/ritonavir will increase the rate of throat-swab SARS-CoV-2 nucleic-acid negative conversion.

The main therapeutic index of this study is the clinical recovery time (after no more than 28 days), which is from the beginning of the study drug intervention treatment to the normalization of body temperature, respiratory symptoms, respiratory rate, and blood-oxygen saturation. In the later analysis, the log-rank method is used to compare the differences in clinical recovery time between the two groups of patients. The sample size of this study is calculated based on the log-rank method by using the log-rank test (Lakatos) (median survival time) module in the PASS 11.0 statistical software (see Additional file: Sample size report” for details).

Based on clinical experience [4, 18], the median clinical recovery time of the patients in the control group is expected to be 8 days, and the median clinical recovery time of patients in the experimental group can be shortened to 4 days (corresponding hazard ratio (HR) = 2.0) 112 patients (56 in each group) will be required to detect this difference with a significant level of *α* = 0.05 (both sides) with 85% confidence interval.

The trial is planned to be enrolled for 90 days, followed up for 28 days, and a final analysis is performed after 78 clinical recovery events occur. It is estimated that the drop-out rate of the experimental group and the control group is 5%.

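### Randomisation is described as stratified by centre, but the primary log-rank test is stated without strata and the Cox model does not name centre

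*Protocol article*

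**What the plan says.** - **Allocation.** Protocol article, Randomization: "Grouping is carried out using a centrally stratified, randomized block method". The parameters of the list are given as "set the number of centers at four, the block size will be four, the number of blocks will be 28". The two arms are of equal size. Centre is the only stratification factor visible. The same section then describes one numbered series of envelopes, 1 to 112, opened in order of enrolment.
- **Primary test.** Analysis of primary outcomes: "The difference between the control arm and the experimental arm will subsequently be determined using the log-rank test". The Sample size section also names the log-rank method, sized with a two-group Lakatos module. Neither place mentions strata.
- **Adjusted model.** A Cox model is added because of "possible confounding factors such as gender and age on the clinical recovery time". The list is introduced by examples and is not closed.
- **Stratified analysis.** This section refers only to throat-swab RT-PCR status. No analysis section mentions centre.

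**The concern.** Blocking within centres makes the arms more alike than chance would. If centre predicts recovery, the treatment difference then varies less between hypothetical repeats of the trial than an unstratified log-rank variance assumes. The test rejects too rarely under the null and gives up power under the alternative. Analysing by the randomisation strata removes that mismatch.

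A centre effect is plausible here, though the article does not quantify it. The Design section says that no concomitant treatment is prohibited, so background care may differ by hospital. The setting includes both outpatients and inpatients. Relief of respiratory symptoms, part of the primary endpoint, is judged locally without blinding.

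**Working it through.** **1. The plan's own figure.** Inputs from Sample size: medians 8 and 4 days, hazard ratio 2.0, two-sided 5%, 85% ("0.05 (both sides) with 85% confidence interval", read as power), 112 patients, 78 events.

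- Schoenfeld: 4(1.960 + 1.036)² / (ln 2)² = 4 × 8.98 / 0.480 ≈ 75 events.
- Freedman: [(2 + 1)/(2 − 1)]² × 8.98 ≈ 81 events.
- Lakatos, coded directly: about 77 to 80 events across dropout assumptions.
- Power at 78 events (Schoenfeld): Φ(√78 × ln 2 / 2 − 1.960) = Φ(1.10) ≈ 86.5%.

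The 78 events are reproduced as the requirement of an *unstratified* log-rank test. The 112 patients are reproduced only if the 5% dropout acts per day, which is a separate matter.

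**2. Layout.** 28 blocks × 4 = 112 patients. If split equally, this is 7 blocks or 28 patients per centre.

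**3. Simulation.** Exponential recovery times with the plan's medians, blocks of four within four centres, censoring at day 28, 5% dropout over 28 days, 8,000 trials per cell. The 78-event analysis is taken when the 78th recovery occurs during 90-day accrual. Monte Carlo standard error is √(0.05 × 0.95/8000) ≈ 0.24 points for size and √(0.8 × 0.2/8000) ≈ 0.45 points for power near 80%.

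The centre SD *s* of the log hazard is an **assumption**, shown over a range. Four equally spaced centre effects with SD *s* span 6*s*/√5 = 2.68*s*. So *s* = 0.25 means a hazard ratio of exp(0.67) ≈ 2.0 between the extreme centres, and *s* = 0.5 means exp(1.34) ≈ 3.8.

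Unstr. = unstratified and Str. = centre-stratified log-rank test. Power is at hazard ratio 2; the last column is stratified minus unstratified.

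| Centre SD | Size, unstr. (full follow-up) | Power, full follow-up: unstr. / str. | Power, 78 events: unstr. / str. | Change from stratifying (full / 78 events) |
|---|---|---|---|---|
| 0 | 5.2% | 94.1 / 92.8% | 84.9 / 82.1% | −1.3 / −2.8 |
| 0.25 | 4.7% | 92.1 / 92.4% | 82.6 / 81.4% | +0.3 / −1.2 |
| 0.5 | 3.7% | 86.8 / 91.9% | 74.6 / 81.7% | +5.1 / +7.1 |
| 0.75 | 2.1% | 75.7 / 90.8% | 65.0 / 82.3% | +15.1 / +17.3 |
| 1.0 | 1.3% | 61.5 / 90.0% | 52.7 / 82.5% | +28.5 / +29.8 |

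The stratified test keeps a size of 5.2 to 5.6% at full follow-up. Full-follow-up power exceeds the nominal 85% because about 102 recoveries are then observed at SD 0.5, not 78.

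**4. Sensitivity.**

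- *Unequal centres (64/24/16/8).* At SD 0.5: 87.3 / 92.0% at full follow-up and 77.3 / 82.2% at 78 events. At SD 0.25: 92.6 / 92.6% and 84.0 / 82.5%. At SD 0: 93.8 / 92.5% and 85.0 / 81.6%.
- *Centre effects drawn from a normal distribution instead of equally spaced.* At SD 0.5, with everyone followed to day 28 (6,000 trials): size 3.9%, power 88.3 / 92.4%. The direction is the same and the loss slightly smaller.

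**The case against.** The strongest objection is scope. This is a condensed article and the analysis plan is not shown. Strata for the log-rank test and the full covariate list could be fixed there. This stands in part. The text contains no contradiction, and a reader who infers that the Cox model excludes centre goes too far, because the list gives examples only. But the article does state the primary test, its sizing and a stratified analysis, and the randomisation factor appears in none of them.

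A reader might also infer that the plain test certainly loses power and that stratifying is free. The documents do not support this. They give no between-centre difference, and with identical centres the unstratified test keeps its level and is the more powerful one. It also matches the way the trial was sized.

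Nor is there a threat to validity: where the unstratified size departs from 5%, it falls below it.

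The single envelope series leaves some doubt whether each centre had its own list. If one list served all sites in order of enrolment, blocks would not balance within centres and the conservatism argument would weaken.

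Finally, the mild/general class is not described as a stratification factor, and the documents give no figure for its effect on recovery. Leaving it unnamed is not an error.

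**Conclusion.** The point holds as a matter of efficiency and of consistency between design and analysis. As written, the primary analysis does not use the factor by which allocation is described as stratified.

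The size of the consequence rests wholly on an assumed centre effect. A clear loss, about 5 to 7 points of power with a true size near 3.7%, appears at a log-hazard SD of about 0.5, roughly a 3.8-fold hazard range between the extreme hospitals. At 0.25 the choice hardly matters, and the unstratified test is slightly ahead at 78 events. At zero, stratifying costs 1.3 points at full follow-up and 2.8 at 78 events.

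The trade is uneven. At 78 events with equal centres, stratified power stays between 81.4 and 82.5% over the whole range, while unstratified power runs from 84.9 down to 52.7%. That makes stratification the safer default when the centre effect is unknown.

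**What to change.** - State that the primary test is the log-rank test stratified by centre, or say why it is not.
- Stratify the Cox model by centre and replace the examples with a closed list named in advance: age and sex, with baseline mild/general class as an optional addition.
- State in the Randomization section whether each centre has its own allocation sequence.
- Because the trial is open-label and already recruiting, record the change before outcomes are compared by arm.

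The cost is a sentence or two in the plan and a line of program code; no new data are needed. The statistical price is about 1 to 3 points of power if the centres do not differ (3.4 points at 78 events with the unequal centre sizes above). At 78 events, power should then be quoted as about 82%, not 85%.

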#### Analysis of secondary outcomes

The analysis of secondary outcomes will be described as explorative outcomes. The rate of treatment success after the completion of therapy and follow-up among the two groups will be compared using the chi-square test or Fisher’s exact test. The time of treatment success after no more than 28 days, the time to normal temperature (calculated from the onset of illness) during the completion of therapy and follow-up will be calculated in each group and compared using the log-rank test.

The rate of SAEs during the completion of therapy and follow-up will be compared among the two groups using the chi-square test or Fisher’s exact test.

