### Design

This is a prospective, open-label, randomized controlled, multicenter clinical study with two arms. Eligible patients are first screened by safety laboratory testing. Patients with diagnosed mild/general COVID-19 infection are randomized to the following two arms at a 1:1 ratio:
Arm 1 (control arm): lopinavir/ritonavir treatment for diagnosed mild/general COVID-19 infection uses lopinavir 800 mg/day and ritonavir 200 mg/day for no more than 10 daysArm 2 (investigation arm): chloroquine phosphate treatment using chloroquine phosphate 1000 mg/day, equivalent to chloroquine 600 mg/day for no more than 10 days

The CRF is shown in Fig. 1. The schedule of treatment visits and data collection (also known as the CRF) is shown in Table 1.

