### Outcomes

The primary outcome is the clinical recovery time of no more than 28 days after the completion of therapy and follow-up. The secondary outcomes include the rate of treatment success after the completion of therapy and follow-up, the time of treatment success after no more than 28 days, the rate of serious adverse events (SAEs) during the completion of therapy and follow-up, and the time to return to normal temperature (calculated from the onset of illness) during the completion of therapy and follow-up.

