### Definitions

#### The clinical recovery time and adverse events

We define the clinical recovery time as the time (in hours, no more than 28 days) from the start of study drug intervention to normalization of body temperature, respiratory symptoms (cough, nasal stuffiness, nasal discharge, etc.), respiratory frequency, and blood-oxygen saturation. Specifically, also meeting the following criteria at the same time:
① No fever: axillary body temperature ≤ 37.2 °C② Relief of respiratory symptoms (72 consecutive hours)③ Respiration rate ≤ 24/min (resting state)④ Fingertip blood oxygen > 94%

Adverse events (AEs) refer to adverse medical events that occur after a patient or clinical trial participant receives a drug, but they are not necessarily causally related to treatment.

Serious adverse events (SAEs) refer to events that require hospitalization, prolonged hospital stay, disability, affect working ability, are life-threatening or fatal, cause congenital malformation and other events that occur during the clinical trial.

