### Participants

#### Inclusion criteria

Age ≥ 18 yearsPatients diagnosed with COVID-19 according to the criteria of the seventh edition of the Treatment Plan of China for new coronavirus pneumonia (URL: http://202.116.81.74/cache/4/03/www.nhc.gov.cn/5d9aa1423a8a577e1cc197a0d3c434d8/ce3e6945832a438eaae415350a8ce964.pdf):
① Epidemiological history:
Within 14 days before the onset of illness, a history of travel or residence in Wuhan and surrounding areas, or other communities with reported casesWithin 14 days before the onset of illness, exposure to a person with COVID-19 infection (positive nucleic-acid test)Exposure to patients with fever or respiratory symptoms from Wuhan and surrounding areas, or communities with case reports within 14 days before illness onsetAggregated disease: two or more cases of fever or respiratory symptoms occurring in a small area, such as home, office, school class, etc., within 2 weeks② Clinical manifestations:
Fever or respiratory-tract symptoms: cough, nasal stuffiness, nasal discharge, etc.Normal or decreased white-blood-cell counts in the early stages of disease; normal or decreased lymphocyte countsMultiple, small, patchy shadows and interstitial changes in the early stages of chest imaging, which are evident in the extrapulmonary zones, and which develop multiple “ground-glass” infiltrations and infiltrates throughout both lungs. In severe cases, pulmonary consolidation may occur, but the formation of pleural effusion is rare③ Confirmed conditions: fulfillment of any one of the epidemiological history items and any two of the clinical manifestation items or three clinical manifestation items if no epidemiological history is available, in addition to meeting one of the following etiological or serological criteria:
Real-time fluorescent RT-PCR detects novel coronavirus nucleic acidThe gene-sequencing results of patients’ specimens (blood, stool, etc.) are highly homologous to those of known novel coronavirusesSerum SARS-CoV-2-specific antibodies IgM and IgG are positive, serum SARS-CoV-2-specific IgG antibodies change from negative to positive or the quantity of IgG in the recovery phase is at least four times higher than in the acute phase (3–5 days after illness onset)Mild or general patients:

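### Time to normal temperature is counted from illness onset and compared by an ordinary log-rank test, which adds pre-treatment days to the outcome and dilutes the treatment contrast.

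*Protocol article*

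**What the plan says.** The protocol article's Outcomes section lists as a secondary outcome "the time to return to normal temperature (calculated from the onset of illness) during the completion of therapy and follow-up". The abstract gives the same time origin. Under Analysis of secondary outcomes it is repeated: "the time to normal temperature (calculated from the onset of illness) during the completion of therapy and follow-up will be calculated in each group", with a log-rank comparison of the arms. No delayed entry is mentioned.

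The primary outcome uses a different clock. Under The clinical recovery time and adverse events, time runs "from the start of study drug intervention to normalization of body temperature" and three other signs, with an axillary temperature of at most 37.2 °C as the temperature criterion.

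Under Design, patients are screened, diagnosed and then "randomized to the following two arms at a 1:1 ratio". Fever is not required at entry: under Inclusion criteria it is one alternative within a single clinical item, "Fever or respiratory-tract symptoms: cough, nasal stuffiness, nasal discharge, etc". On the status of these outcomes the article says: "The analysis of secondary outcomes will be described as explorative outcomes".

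**The concern.** One sign, normalisation of temperature, is measured on two clocks, and no reason is given. On the onset clock, each patient's time is the sum of a delay before treatment and a time on treatment. Only the second part can respond to the drug. For a patient still febrile at entry, the first part is event-free by construction.

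An ordinary log-rank test on this scale compares, on each day since onset, everyone whose onset-based time has not yet ended. That set includes patients who had not yet been randomised on that day, and it puts patients with different lengths of exposure side by side. At stake is how well this comparison can show a temperature effect, and whether it can be read alongside the primary outcome.

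**Working it through.** **1. The plan's own figure.** The Sample size section concerns the primary outcome: medians of 8 and 4 days, HR 2.0, 112 patients, 78 events, and "0.05 (both sides) with 85% confidence interval", read here as 85% power.
- Schoenfeld: 4 × (1.960 + 1.036)² / (ln 2)² = 4 × 8.98 / 0.480 ≈ 75 events.
- Freedman: 8.98 × ((1 + 2)/(1 − 2))² = 8.98 × 9 ≈ 81 events.
- The stated 78 lies between them. Power at 78 events: Φ(√(78/4) × 0.693 − 1.960) = Φ(1.10) ≈ 0.865.

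The event count is consistent. No figure is given for the temperature outcome, so what follows illustrates the mechanism and does not check a stated number.

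**2. Inputs.** From the documents: 56 per arm, 1:1 allocation, two-sided 5% level, 28 days of follow-up. Assumed: a gamma-distributed delay from onset to drug with mean 3 to 7 days, exponential times to normal temperature after drug start, and all temperature medians. The 8 and 4 days are borrowed from the primary composite. Temperature is only one of the four criteria that the composite needs together, so it should normalise no later than the composite. That is why shorter medians were also tried.

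**3. Risk sets.** Take delays of 3 and 7 days, both within the assumed range. On day 5 after onset the first patient has had 5 − 3 = 2 days of drug; the second is 7 − 5 = 2 days short of starting. The onset-clock log-rank test treats them as comparable on that day.

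**4. Why the loss depends on the medians.** An exponential time has SD = median / ln 2. Add an independent delay with SD 3 days (ignoring censoring):
- Median 8: 11.5 becomes √(11.5² + 3²) ≈ 11.9 days.
- Median 4: 5.8 becomes √(5.8² + 3²) ≈ 6.5 days.
- Median 2: 2.9 becomes √(2.9² + 3²) ≈ 4.2 days.

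The shorter the fever after treatment starts, the more the delay dominates.

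**5. Simulated power, mean delays 3 to 7 days, all patients febrile at entry.**

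| Assumed medians (days) | From drug start | From onset |
|---|---|---|
| 8 vs 4 | about 95% | 90–93% |
| 4 vs 2 | 94–95% | 72–89% |
| 4 vs 2.67 | 54–55% | 37–49% |

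A separate run at 8 vs 4 days (600 trials per scenario) included a more variable delay, mean 7 and SD 6 days. In that case power from onset fell to 84%, and the estimated HR fell from 2.0 to 1.76.

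**6. Type I error.** With no treatment effect, rejection was 5.5–5.8% from onset and 5.1–5.4% from drug start, both near nominal.

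**7. Patients already afebrile at D0 (conditional).** Suppose they were counted as events before treatment, with post-drug medians of 8 and 4 days for the rest:

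| Assumed share afebrile | Febrile only, from drug start | Everyone, from onset |
|---|---|---|
| 20% | 0.89 | 0.63–0.75 |
| 40% | 0.78 | 0.39–0.53 |

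The middle column also shows what restricting to febrile patients costs, compared with about 0.94 when all are febrile.

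**The case against.** The strongest defence is that randomisation balances the delay on average. Event-free time before entry arises equally in both arms, the test remains valid, and total duration of fever has a clinical meaning. All of this stands. The outcome is also exploratory, and the primary outcome already includes temperature on the treatment clock, so the main conclusion does not depend on it.

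At the only medians that the documents give, the loss is just a few percentage points for most delays tried. The larger losses rest on medians and delays that are assumed. That also stands, and it limits the claim about size.

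A reader might infer three stronger things that the documents do not support:
- *That recoveries before treatment are counted as events.* No text says so. The outcome is tied to the period of therapy and follow-up, which points towards events seen on study. How patients already afebrile at D0 are handled can properly be left to an analysis plan that is not shown, so its absence here is not an error.
- *That a chance imbalance in delay would pass for a drug effect.* Such imbalance is covered by the test's error rate, which stays near 5%.
- *That the times cannot be interpreted.* They describe fever duration from onset. They are a blunter measure of the treatment effect.

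None of this removes the point about the time origin, which is a stated rule and differs from the one used for the primary outcome.

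**Conclusion.** The point holds as a matter of time origin. Starting the clock at illness onset with an ordinary log-rank test puts days in the outcome that the drug cannot influence, and it mixes patients at different times on treatment. The result is a diluted contrast and lower power, with no tilt towards either arm and no material inflation of type I error.

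The loss ranges from a few percentage points at 8 vs 4 days to roughly 5 to 23 points at 4 vs 2 days. It depends on assumed delays of mean 3 to 7 days, assumed medians and exponential times. It would be larger if patients already afebrile at D0 were counted as events before treatment, but that is conditional. The change is worth making because it is specific and small; the primary analysis is unaffected.

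**What to change.** Define time to normal temperature from randomisation or start of study drug, as the primary outcome does, among patients with axillary temperature above 37.2 °C at D0. Make the change in the abstract, in Outcomes and in Analysis of secondary outcomes. If the onset-based time is of interest, keep it as a descriptive summary by arm, or analyse it on the onset scale with delayed entry at randomisation.

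The cost is more than a wording change in an analysis plan. It amends the protocol definition of one exploratory secondary outcome while recruitment is described as ongoing in an open-label trial, so the amendment should be dated and made without sight of results by arm. Patients afebrile at D0 leave this one analysis, with the loss of precision shown in step 7. The two time origins already in the protocol require dates of onset and of first study drug. The data collection schedule is not shown, so it should be confirmed that D0 temperature is recorded.

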**Discussion:**

This experiment should reveal the efficacy and safety of using chloroquine versus lopinavir/ritonavir for patients with mild/general COVID-19 infection. If the new treatment including chloroquine shows a higher rate of throat-swab SARS-CoV-2 real-time fluorescent reverse transcription polymerase chain reaction (RT-PCR) negativity and is safe, it could be tested as a future COVID-19 treatment.

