### Efficacy outcomes

Comparisons will be performed using two-sided tests with a statistical significance level of 5% unless stated otherwise.

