### Safety assessment

All AEs according to the Common Terminology Criteria for Adverse Events (CTCAE) will be collected and documented, regardless of severity, seriousness, or relationship to the study drug. We will summarize all AEs, include AE frequency and percentage, and 95% CIs and compare the occurrence rate of AEs in relationship to the study drug and the severity of the two arms using the chi-square test or Fisher’s exact test.

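### The forward conclusion requires chloroquine to be safe, but the only between-arm safety analysis stated is a significance test with low power at 56 per arm; report the risk difference with its interval and bound the wording by it

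*Protocol article*

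**What the plan says.** The Discussion paragraph of the abstract sets two conditions for going forward, one on RT-PCR results and one on safety: if chloroquine shows a higher rate of "negativity and is safe, it could be tested as a future COVID-19 treatment". The main Discussion also names safety as a purpose of the trial.

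The safety methods are these:

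- **Serious adverse events** (Analysis of secondary outcomes): "The rate of SAEs during the completion of therapy and follow-up will be compared among the two groups using the chi-square test or Fisher’s exact" (last word omitted). The same section labels all secondary outcomes as exploratory.
- **Adverse events** (Safety assessment): frequency, percentage and 95% confidence intervals are to be summarised. The plan will then "compare the occurrence rate of AEs in relationship to the study drug and the severity of the two arms using the chi-square test or Fisher’s" (last two words omitted).
- **Level of testing** (Efficacy outcomes): "Comparisons will be performed using two-sided tests with a statistical significance level of 5% unless stated otherwise". The abstract lists the SAE rate among the secondary outcomes and then gives the same two-sided 5% level for comparisons in general.
- **Size** (Sample size): "112 patients (56 in each group) will be required to detect this difference", the difference being a hazard ratio of 2.0 in clinical recovery time. No SAE rate, safety margin or safety power is given.

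**The concern.** A test of no difference can show harm when the harm is large, but a non-significant result from a small trial says little about its absence. A statement of safety needs an upper bound on the excess risk. The primary outcome gets a hazard ratio with a 95% interval; the SAE comparison gets a test and no effect estimate. The 95% intervals under Safety assessment attach to the AE frequency and percentage, so they most naturally describe each arm alone.

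At stake is the safety half of the forward conclusion. If the report contains only a non-significant p-value, readers cannot see how large an excess of serious events is still compatible with the data. At this sample size that excess can be large.

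**Working it through.** **Inputs.** From the article: 56 per arm (Sample size), allocation 1:1 (Design), two-sided 5% (Efficacy outcomes), drop-out 5%, so about 56 × 0.95 = 53 evaluable per arm (Sample size). Control SAE rates are my assumption, taken from 2% to 20%.

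**1. The plan's own figure.** Sample size gives 78 events, HR 2.0 and "0.05 (both sides) with 85% confidence interval", where 85% is evidently the power.

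- Schoenfeld: power = Φ(√78 × ln 2 / 2 − 1.96) = 86.5%
- Freedman: power = Φ(√78 / 3 − 1.96) = 83.7%

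These lie on either side of 85%, so the event count is consistent with the recovery-time endpoint. Nothing in the calculation concerns safety.

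**2. Power of the safety tests.** For each pair of true rates, I summed the binomial probabilities of all 57 × 57 outcome pairs for which the test gives p ≤ 0.05. I used two-sided Fisher and uncorrected chi-square tests, 56 per arm.

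| Control vs chloroquine | Fisher | Chi-square |
|---|---|---|
| Doubling: 2% vs 4% | 1% | 7% |
| 5% vs 10% | 8% | 16% |
| 10% vs 20% | 22% | 32% |
| 15% vs 30% | 39% | 49% |
| 20% vs 40% | 57% | 65% |
| Tripling: 2% vs 6% | 5% | 16% |
| 5% vs 15% | 29% | 43% |
| 7% vs 21% | 47% | 59% |
| 10% vs 30% | 69% | 78% |
| 15% vs 45% | 92% | 95% |

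With 53 per arm the power is slightly lower: 7% to 15% for 5% vs 10%, and 27% to 41% for 5% vs 15%. For scale, 80% power at 5% vs 10% would need about 435 per arm: [1.96√(2 × 0.075 × 0.925) + 0.842√(0.0475 + 0.09)]² / 0.05² ≈ 435.

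In counts, Fisher's test reaches p ≤ 0.05 only from 6 vs 0, 8 vs 1 or 10 vs 2 events.

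**3. What an interval would show.** The Newcombe limits for d = p₁ − p₀, with Wilson limits (l, u) for each arm, are

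- lower: d − √[(p₁ − l₁)² + (u₀ − p₀)²]
- upper: d + √[(u₁ − p₁)² + (p₀ − l₀)²]

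Take 8/56 vs 3/56, so p₁ = 0.143 (0.074, 0.257), p₀ = 0.054 (0.018, 0.146) and d = 0.089.

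- lower: 0.089 − √(0.069² + 0.092²) ≈ −0.026
- upper: 0.089 + √(0.115² + 0.035²) ≈ 0.209

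Fisher's p is 0.20, yet an excess of 21 points is not excluded.

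| Observed, chloroquine vs control | 95% CI for the difference (points) |
|---|---|
| 9/56 vs 3/56 | −1 to +23 |
| 8/56 vs 3/56 | −3 to +21 |
| 3/56 vs 3/56 | −10 to +10 |
| 0/56 vs 0/56 | −6 to +6 |

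For one arm alone, no events in 56 still allows a true rate up to 1 − 0.025^(1/56) = 6.4%.

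**The case against.** Several points on the other side are fair.

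- **A reader might infer that p > 0.05 will be taken to mean safe.** The article does not say so. It names tests without saying what a null result would mean, and it leaves safety undefined. What remains is that no other between-arm basis for the word is offered.
- **A reader might also infer that any doubling or tripling would usually be missed.** That depends on a background rate the article does not give. Doubling is more likely detected than missed at 20%, and tripling is usually detected from about 10%. The SAE definition is broad (it includes a prolonged hospital stay), so a low background rate cannot be presumed. On the other hand, enrolment is limited to mild or general disease and excludes arrhythmia and chronic heart disease, so low rates are plausible.
- **Tests are not the whole of the safety plan.** Adverse events are summarised with 95% intervals, and a Data and Safety Monitoring Board reviews data during the trial. Both are true. But the intervals read as per-arm, and the Board's role is to advise on conduct, not to give a criterion for the final statement.
- **The claim is modest.** SAEs are exploratory, and the stated consequence is only that chloroquine could be tested further. This limits the harm. It does not give an exploratory test the ability to support a safety condition.
- **Interval methods belong in an analysis plan, and low power for SAEs is common in trials sized on efficacy.** The choice of interval method could indeed sit there, and low power alone would not be a finding. The point here is narrower: the article fixes a method and a conclusion, and the one cannot support the other.

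**Conclusion.** The concern holds in limited form. The safety condition in the abstract has no stated criterion, and the only between-arm safety method given is a chi-square or Fisher test. At 56 per arm that test cannot support a statement of safety. Under assumed control rates, both tests miss a doubled SAE rate more often than not up to about 15%, and a tripled rate up to about 5%. Tripling is about even at 7% and usually detected from about 10%. The interval results do not depend on an assumed rate: even equal counts of 3 per arm leave an excess of about 10 points open, and no events in either arm leaves about 6.

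This does not show that the sponsor intends to read a null test as safe, nor that a larger trial is needed. It is a low-cost improvement in analysis and wording.

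**What to change.** 1. In Analysis of secondary outcomes and in Safety assessment, report the SAE and AE risk difference (chloroquine minus lopinavir/ritonavir) with a two-sided 95% confidence interval, by the Newcombe or Miettinen-Nurminen method. Keep the chi-square or Fisher p-values as descriptive.
2. State in the same place that a non-significant test is not evidence of safety.
3. In the Discussion paragraph of the abstract, replace the bare safety condition with wording bounded by that interval, for example: *no safety signal was seen; an SAE excess of up to X percentage points (upper 95% limit) is not excluded*. A phrase such as *judged acceptable* should be avoided unless the acceptable limit is fixed in advance, because it is as undefined as the present wording.

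The cost is a few sentences and one extra interval per safety table, with no extra patients, visits or data. The downside is a more modest safety claim, since at this size an excess of roughly 6 to 10 points will usually remain open even when the observed counts are equal and low.
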